### Data collection

#### Data collection training

Data collectors will consist of undergraduate and graduate students from nutrition, public health or other related fields, as well as registered dietitian nutritionists. All data collectors will undergo an 8-hour data collection training, which will include didactic sessions followed by role-playing to practice techniques and become familiar with the instruments. At the end of the 8-week intervention prior to post-test data collection, data collectors will complete a 2-hour review training to reacquaint themselves with the instruments and learn additional post-test data collection feedback surveys.

#### Impact measures

Child-caregiver dyads and youth mentors will be interviewed at baseline and post-intervention using the Camp NERF Child Assessment Form, Camp NERF Adult Assessment Form, and Camp NERF Youth Mentor Assessment Form, respectively. Each assessment form consists of validated nutrition, physical activity, and mental health questionnaires. Three (2 weekdays and 1 weekend day) 24-hour dietary recalls will be conducted for both the children and youth mentors. Heights, weights, blood pressure, and waist circumference measurements will be taken for the children and youth mentors. Caregivers will self-report height and weight. Table 2 provides the Camp NERF Evaluation Chart and outlines all validated surveys and outcomes measured for participants.

**Table 2 Tab2:** Camp NERF evaluation chart for children, caregivers, and youth mentors

Outcomes	Goal	Measure	b0	T1
Child Outcomes				
Nutrition				
Food Attitudes and Preferences	Increase preference for fruits and vegetables	Fruit and Vegetable Preferences *Domel 1993* ^85^	X	X
Dietary Intake	Increase quality of diet (increase fruit and vegetable intake (quantity and variety), decrease intake of foods high in solid fats and added sugars; decrease sugar-sweetened beverages)	Caregiver-assisted 24-hour diet recall *Burrows et al 2010* ^86^ *Baxter et al 2003* ^87^ *Baxter et al 2009* ^88^	X	X
Physical Activity				
Physical activity level and sedentary time	Increase estimated active time and decrease estimated time in sedentary behavior	3rd-5th^:^ SPAN questionnaire *Hoelscher et al 2010* ^89^	X	X
Mental Health				
Self-concept	Increase positive affect	PANAS Survey *Laurent et al 1999* ^90^	X	X
	Decrease negative affect			
	Retain positive changes in self-concept			
Social Support				
Social Support for Food and Physical Activity Habits	Increase social support for food and physical activity habits	Social Support Scale for Food and Physical Activity Habits	X	X
		*Gadhoke 2015* ^91^		
Social Support for Healthy and Unhealthy Eating	Increase social support for healthy eating and decrease social support for unhealthy eating	Social Support Scale for Healthy and Unhealthy Eating *Fitzgerlad 2013* ^92^	X	X
Biometrics				
Height and Weight	Prevent unhealthy weight gain	Hopkins Road Rod Portable Stadiometer (Height) BalanceFrom High Accuracy Digital Scale (Weight) 2000 CDC sex-specific BMI-for-age growth chart^93^	X	X
Waist Circumference	Prevent increase in waist circumference	MyoTape tape measure CDC Waist Circumference Tables ^94^	X	X
Blood Pressure	Prevent increase in blood pressure	Panasonic Portable Blood Pressure Monitor NHBLI Standardized Blood Pressure Tables ^95^	X	X
Youth Mentor Outcomes				
Nutrition				
Food Attitudes and Preferences	Increase preference for fruits and vegetables	Fruit and Vegetable Preferences *Domel 1993* ^85^	X	X
Dietary Intake	Increase quality of diet (increase fruit and vegetable intake (quantity and variety), decrease intake of foods high in solid fats and added sugars; decrease sugar-sweetened beverages)	Youth Mentor reported 24-hour diet recall *Lindquist et al 2000* ^96^	X	X
Physical Activity				
Physical activity level and sedentary time	Increase estimated active time and decrease estimated sedentary time	SPAN questionnaire *Hoelscher et al 2010* ^89^	X	X
Mental Health				
Self-concept	Increase positive affect	PANAS Survey *Laurent et al 1999* ^90^	X	X
	Decrease negative affect			
	Retain positive changes in self-concept			
Social Support				
Social Support for Food and Physical Activity Habits	Increase social support for food and physical activity habits	Social Support Scale for Food and Physical Activity Habits *Gadhoke 2015* ^91^	X	X
Social Support for Healthy and Unhealthy Eating	Increase social support for healthy eating and decrease social support for unhealthy eating	Social Support Scale for Healthy and Unhealthy Eating *Fitzgerlad 2013* ^92^	X	X
Biometrics				
Height and Weight	Prevent unhealthy weight gain	Hopkins Road Rod Portable Stadiometer (Height) BalanceFrom High Accuracy Digital Scale (Weight) CDC sex-specific BMI-for-age growth chart^93^	X	X
Waist Circumference	Prevent increase in waist circumference	MyoTape tape measure CDC Waist Circumference Tables 94	X	X
Blood Pressure	Prevent increase in blood pressure	Panasonic Portable Blood Pressure Monitor NHBLI Standardized Blood Pressure Tables 95	X	X
Caregiver Outcomes				
Nutrition				
Caregiver Self-Efficacy	Improve caregiver self-efficacy to make healthy choices	Self-efficacy to make healthy choices *Bohman 2014* ^97^	X	X
Dietary Intake; Home Food Environment	Increase purchase and consumption of healthy foods; decrease purchase and consumption of unhealthy foods	Home Food Inventory *Fulkerson 2008* ^98^	X	X
Physical Activity				
Leisure Time Exercise	Increase engagement in leisure time exercise	Leisure Time Exercise Questionnaire *Godin & Shepherd 1985* ^99^	X	X
	Retain positive changes in leisure time exercise			
Anthropometrics				
Height and Weight	Prevent unhealthy weight gain	Self-report	X	X
Weight	Prevent unhealthy weight gain	Self-report	X	X

b0 = baseline; beginning of summer

t1 = post-intervention; end of summer

Interviews will be conducted at the home of the participants, the site, or another community location and are estimated to take approximately 30 min, 10 min, and 20 min to complete for the child, caregiver, and youth mentor, respectively. All assessment forms will be data collector-administered, where the data collector will read each question from the assessment form verbatim including all possible responses and record the participants’ response. If the participant provides an ambiguous response, the data collector will ask necessary questions to probe for a specific response. For younger children, caregivers will be asked to assist in completing and verifying responses from the child interview when deemed necessary.

#### Data analysis

The intervention will be tested by comparing change from baseline to post-intervention in diet quality, physical activity, mental health, and anthropometric outcomes for child participants (hypothesis 1.1) and psychosocial, physical activity, and anthropometric outcomes for adults (hypothesis 2.1). For each outcome variable of interest (Table 2), a mixed effects linear regression model will be fitted with site-type as the primary predictor. Other covariates will include race/ethnicity, income, and attendance, as well as baseline zBMI for all models that do not include weight status as the primary outcome. Using a mixed effects linear regression model allows us to capture the contributions of two sources of variability: (1) a between-site variability and (2) a between-subject or within-site variability. Impact of Camp NERF on Youth Mentors will be tested by comparing change from baseline to post-intervention in diet quality, physical activity, mental health, and anthropometric outcomes (hypothesis 3.1) using multiple linear regression analyses.

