The rise and current status of obesity in the US has occurred at such a rapid rate that it cannot solely be attributed to biological changes [12]. While obesity rates have been rising over the past several decades, the US food environment has also been changing drastically, providing convenient access to an abundance of inexpensive, highly palatable, energy-dense foods [13]. Thus, the current prevalence of childhood obesity and demonstrated increase in obesity during the summer months could be a response to children’s increased exposure to the food environment [13], which they have less frequent access to during the school year, and lack of structured physical activity. Schools play a critical role in promoting healthy diet and physical activity behaviors during the academic year [14]. During the summer months, however, children lose access to this structured environment (e.g., provision of healthy snacks and meals; opportunity for structured and unstructured physical activity; nutrition, physical activity, and health related policies and programs).

The United States Department of Agriculture (USDA) aims to provide access to healthy, nutritious meals to children during the summer months through the USDA Summer Food Service Program (SFSP) [15]. Unfortunately, attendance at USDA SFSP sites, especially open sites, and amount of meals served tends to be low. According to the Food Research Action Center, only 15.8 % of free or reduced-cost school lunch participants received lunch in the summer of 2015 nationally [16]. In Ohio, only 10.8 % of free or reduced-cost school lunch participants participated in the SFSP [17]. Several stakeholders have hypothesized that these low numbers are due to a lack of structured programming at the sites to attract children. Few efforts have been directed at designing evidence-based nutrition and physical activity programs to equip underserved children with the necessary knowledge, skills, and other resources to prevent excess weight gain during the summer recess.

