#### Process evaluation and environmental assessment

A Camp NERF Site Environmental Assessment Form was developed for this study and will be completed at baseline, mid-intervention (4 weeks), and post-intervention. The purpose of this form is to assess the demographic (i.e. predominant race/ethnicity of the staff at the sites), food environment (i.e. presence of vending machines, concession stands, and healthfulness of available foods), and physical activity environment (i.e. access to a gym, outdoor playground, equipment, etc.) characteristics of the sites. This information will be used in post-hoc analyses to determine if characteristics (i.e., access to a computer room) may have contributed to outcomes.

A Camp NERF Daily Process Evaluation Form was developed for this study and will be completed by trained process evaluators, who will not be involved with intervention implementation. This form assesses feasibility, fidelity, and acceptability of the intervention programming, assessment of food served, adherence to the USDA SFSP menus, and participant attendance.

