#### Caregiver engagement

The caregiver engagement component will be in the form of a texting program that will utilize a mass messaging platform, social media (Facebook and Instagram), and traditional education materials. Adult caregivers of Camp NERF participants in the Enhanced Care group will be provided the option to receive three text messages each week over the course of the intervention. The first message each week will introduce the main nutrition topic that was presented to their child during programming but will encourage completion of a specific family nutrition goal to be attained by the end of the week. For example, the message preceding the fourth week of programming may read as follows: “Today at Camp NERF, your child learned about healthy fast food items. Are you in for trying healthier items at fast food restaurants? Please reply with ‘Yes’ or ‘No’.” The second message content will consist of either a strategy to assist the caregivers in reaching the weekly goal or educational information related to the topic of the week. The final message will inquire about achievement of the goal-setting challenge proposed at the start of the week.

Social media outlets such as Facebook, Twitter, and Instagram will be offered as an alternative means for caregivers to receive insight on the nutrition topic for the week. Images or videos will be added to the websites for caregivers to view and interact with counselors as well as other caregivers. Nutrition topics will be explored in greater depth, such as links to simple food recipes, news items, and recent educational articles related to the weekly topic.

In addition to the text-messaging and social media campaigns, traditional educational materials also will be disseminated to caregivers at the Enhanced Care sites weekly. These educational materials are adapted from the CATCH Kids Club Healthy Habits and Nutrition curriculum handouts for parents [26]. The handouts are modified to include concepts from the CATCH Physical Education curriculum and the COPE curriculum [26, 27]. Child participants will be given handouts at the end of the week to take home to their caregivers.

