Several challenges or limitations have been identified. Engagement from caregivers in the target population may be a challenge, as it is a common issue with intervention research involving underserved families [84, 85]. However, this study was developed and designed to overcome this barrier. The research team and community collaborators will be present in the participating neighborhoods for several years throughout the development of the project. High-school aged students from the intervention communities will be engaged as Youth Mentors and will assist with education delivery throughout the entirety of the program. Traditional (educational handout materials) and innovative (text messaging and social media) strategies will be utilized to inform parents about the programming and encourage participation. Another limitation is the lack of a true negative control group. Because Camp NERF will be coupled with the USDA SFSP, a federal child nutrition program, the statutory right for participation applies. Ethically, the research team cannot ask children and families to not participate at the open SFSP sites. Additionally, recruitment methods are not designed to seek participants who do not intend to attend the SFSP sites during the summer.

In summary, Camp NERF builds on successful childhood obesity prevention interventions which include nutrition and physical activity components, concurrent knowledge and skill building, coupling of the intervention curriculum to availability of healthy foods, and opportunity for physical activity and play [18, 86]. Studying the impact of such an intervention over the summer months will provide valuable information in tackling a time period during which children may be at increased risk for excessive weight gain.

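### Adjusting the child and caregiver models for attendance, which is measured after randomisation, biases the arm comparison to the extent that attendance differs by arm

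*Protocol article*

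**What the plan says.** The Data analysis section sets out one model form for the child and caregiver outcomes: "For each outcome variable of interest (Table 2), a mixed effects linear regression model will be fitted with site-type as the primary predictor". It then fixes the adjustment set: "Other covariates will include race/ethnicity, income, and attendance", with baseline zBMI added where weight status is not the outcome. No model without attendance is described, and attendance is not labelled secondary, exploratory or dose-response. The Youth Mentor regressions are described separately, with no covariates and no arm comparison.

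Attendance comes from the Daily Process Evaluation Form, which covers "assessment of food served, adherence to the USDA SFSP menus, and participant attendance". The Research design section expects 64 h of direct exposure per child and treats this as the dose that should change behaviour, so attendance measures the dose received.

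Hypotheses 1.1 and 2.1, at the end of the Background, state that outcomes will improve more at Enhanced Care sites than at Standard Care and Active Control sites.

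Some components are described only for Enhanced Care. On texting, the Caregiver engagement section says: "Adult caregivers of Camp NERF participants in the Enhanced Care group will be provided the option to receive three text messages each week". The same section describes weekly handouts for caregivers at Enhanced Care sites, and the Intervention section places Youth Mentors at those sites. The Discussion says of the handouts, texts and social media that these "strategies will be utilized to inform parents about the programming and encourage participation".

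**The concern.** Randomising sites protects a comparison of the arms as assigned. It does not protect a comparison of children who turned out to attend equally often, because attendance arises after assignment. Two things can go wrong when it enters the model.

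- **Part of the effect is removed.** If one arm draws children in more often and turnout helps the outcome, that benefit belongs to the effect of assignment. Holding attendance fixed takes it out.
- **Confounding enters.** Family motivation, for example, may drive both turnout and outcome. If attendance also differs by arm, children with equal attendance in different arms then differ in motivation, and the site-type coefficient picks that up.

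These models are the only arm comparisons described for both comparative hypotheses, so no unaffected analysis is available to fall back on.

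**Working it through.** **Inputs from the article (Research design).** SD 1.03; target difference 0.5, taken here as BMI z; 20 children per site; 20% attrition; 12 sites in three arms; one-sided alpha 0.05; about 70% power. Four sites per arm is an assumption of equal allocation. There are no figures on attendance.

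**The plan's own figure.** Power = Φ(0.5 / (SD × √(2/n)) − 1.645).

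| SD of change | n per arm | Power |
|---|---|---|
| 1.03 | 64 (after attrition) | 86.5% |
| 1.03 | 80 | 92.3% |
| 1.03 × √2 = 1.457 | 80 | 70.1% |

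Of these readings, only the last reproduces the stated power. The point here does not depend on that figure, because attendance is not among its stated inputs. It does show that the role of 1.03 is uncertain.

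**Bias formula.** Let τ be the effect of assignment, d the arm difference in mean attendance in within-arm SD units, and s the within-arm slope of the outcome on attendance per SD. In large samples the coefficient adjusted for attendance is τ − s × d, so the bias is −s × d. With within-arm correlation r, |s| = r × SD and the size of the bias is r × d × SD.

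**Illustration with SD 1.03 (r and d are assumed).**

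| r | d | Bias (BMI z) | Share of 0.5 |
|---|---|---|---|
| any | 0 | 0 | 0% |
| 0.1 | 0.2 | 0.021 | 4% |
| 0.2 | 0.5 | 0.103 | 21% |
| 0.3 | 0.5 | 0.154 | 31% |

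If the SD of change were 1.457, the last row would be 0.3 × 0.5 × 1.457 = 0.22, or 44%.

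**Direction.** Lower BMI z is better, so a beneficial τ is negative. Assume a direct arm effect of −0.3, an attendance effect of −0.2 per SD and d = 0.5. The effect of assignment is −0.3 + (−0.2 × 0.5) = −0.40, and the adjusted model returns −0.30. Now add an unmeasured family factor with coefficient −0.3 that accounts for half the within-arm variance of attendance. The slope becomes −0.2 − 0.15 = −0.35, and the adjusted model returns −0.40 + 0.175 = −0.225.

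**Under a true null.** A simulation used 64 per arm, SD 1.03, 4,000 runs and a family factor with coefficient −0.5. The two-sided error of the adjusted model was 4.8% at d = 0, 10.8% at d = 0.5 and 23.9% at d = 1.0. Without attendance it stayed at 4.9% to 5.1%. The extra rejections go against Enhanced Care: at d = 0.5 the expected shift is 0.25 × 0.5 = +0.125. The residual SD is √(1.03² − 0.25²) = 0.999, and the standard error is 0.999 × √(2/64) × √1.0625 = 0.182, so the shift is 0.69 standard errors. The one-sided error in favour of Enhanced Care is then Φ(−1.645 − 0.69), about 1%.

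**The case against.** The strongest reply is that attendance may not differ by arm, in which case the bias is zero. All three arms run 2 days a week for about 4 hours a day over 8 weeks at open meal sites, and the active control was chosen so that programme type could be separated from exposure to structure. The article never predicts an arm difference in attendance. This stands, and it is why the point is conditional.

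A reader might take the Background as proof of a difference, since it says: "Several stakeholders have hypothesized that these low numbers are due to a lack of structured programming at the sites to attract children". It does not serve. That remark contrasts sites with and without structured programming, and here every arm receives it.

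The Discussion's remark about encouraging participation sits in a paragraph on caregiver engagement. The participation meant may be the caregivers' own, and the texts described concern nutrition topics and family goals. The route from Enhanced-only components to child attendance is therefore an inference, though a reasonable one.

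A reader might also infer that every model in the trial is affected, or that the plan invites a false claim of efficacy. The Youth Mentor regressions estimate no arm effect. On the mechanism the article suggests, the distortion runs against Enhanced Care. The opposite sign would need an assumption that the article does not supply.

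Adjustment could be defended as a way to isolate content from exposure. The active control already does that by design, without conditioning on something that happens after randomisation.

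Finally, a fuller analysis plan may exist. The covariate list, however, is a stated rule and not an omission left for another document to fill.

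**Conclusion.** The point holds in conditional form. In the child and caregiver mixed models, the site-type coefficient does not in general estimate the effect of assignment that hypotheses 1.1 and 2.1 ask about; it is biased to the extent that attendance differs by arm. A difference is plausible because of the components described for Enhanced Care, but it is not established. The likelier harm is understatement of the Enhanced Care effect and lost power, in a design with a stated power of only about 70%. This rests on Enhanced Care raising attendance and on attendance or family motivation improving outcomes.

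The range of 0 to about 0.15 BMI z (0% to 31% of the target) is illustrative. The correlation and the arm difference are both assumed, it covers BMI z only, and it scales with the SD used. The article does not support a statement that the estimates are certainly biased, or by a known amount.

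**What to change.** In the Data analysis section:

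1. Delete attendance from the covariates of the primary child and caregiver efficacy models, and compare participants by their site's randomised arm.
2. Report attendance by arm as a process outcome, which also shows whether the arms differed.
3. Keep any attendance-adjusted or dose-response model as a secondary analysis labelled non-randomised.

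This changes a sentence or two and needs no new data, because attendance is already recorded daily. The stated power is unaffected. How participants without a post-test are handled is a separate question that this change does not settle.

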**Fig. 2 Fig2:**
[figure not shown]
Overview of the Camp NERF Treatments

Power was calculated using change in BMI z-score as the outcome of interest. Based on the results from previous pilot test [31, 32], we assume that between-subject variation is normally distributed with a standard deviation of 1.03 and that between-site variation (nested within treatment group) is negligible. Under these assumptions, recruiting 20 subjects per site (planning for 20 % attrition) provides approximately 70 % power to detect a difference of 0.5 points in change in BMI between the treatment group and either of the two control groups using a one-sided test at alpha = 0.05. The model used is described further in the Data Analysis section.

USDA SFSP open feeding sites operate 5 days a week from mid-June through the beginning of August. Their hours of operation will be approximately 9:00 AM – 3:00 PM, although these times vary slightly by site. Camp NERF program (Enhanced Care, Standard Care, or Active Control) will occur 2 days per week for approximately 4 hours each day. This is expected to equate to 64 h of direct exposure per child, a sufficient dose for eliciting behavior change in the targeted outcomes [33–42]. Table 1 provides an overview of a sample day at an Enhance Care site.

**Table 1 Tab1:** Camp NERF daily curricula delivery schedule at enhanced care sites

Time	Grades K-2	Time	Grades 3–5
8:30 AM	Arrival; Engage with participants before and during breakfast	8:30 AM	Arrival; Engage with participants before during breakfast
10:00 AM	Nutrition Education	10:00 AM	Physical Education
10:00 AM	Discussion	10:00 AM	*Warm-up*
10:10 AM	*Learning Activity*	10:05 AM	*Go Fitness*
10:25 AM	*Physical Activity*	10:20 AM	*Go Activity*
		10:40 AM	*Cool-down*
10:45 AM	Mental Health	10:45 AM	Mental Health
11:15 AM	Physical Education	11:15 AM	Nutrition Education
11:15 AM	*Warm-up*	11:15 AM	Discussion
11:20 AM	*Go Fitness*	11:25 AM	*Learning Activity*
11:35 AM	*Go Activity*	11:40 AM	*Physical Activity*
11:55 AM	*Cool-down*		
12:00 PM	Lunch; Lunchtime Engagement and Trivia	12:00 PM	Lunch; Lunchtime Engagement and Trivia

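### The change-score models name no own-baseline covariate, and baseline zBMI is expressly left out of the weight-status models: a loss of efficiency, not a bias

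*Protocol article*

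**What the plan says.** All of the following is in the protocol article.

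- **Response (Data analysis).** "The intervention will be tested by comparing change from baseline to post-intervention". This covers the child outcomes of hypothesis 1.1 and the adult outcomes of hypothesis 2.1.
- **Model (Data analysis).** For each outcome in Table 2, "a mixed effects linear regression model will be fitted with site-type as the primary predictor".
- **Covariates (Data analysis).** "Other covariates will include race/ethnicity, income, and attendance", and then baseline zBMI "as well as baseline zBMI for all models that do not include weight status as the primary outcome".
- **Power (Research design, after Figure 2).** "Power was calculated using change in BMI z-score as the outcome of interest", with a pointer to the model in the Data analysis section.
- **Availability of baselines (Table 2).** Every listed outcome is marked for collection at baseline and post-intervention.

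Baseline zBMI therefore enters every model except those in which it is, or is close to, the outcome's own baseline. The text does not say whether waist circumference counts as weight status. On either reading, the waist model has no baseline waist term named.

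**The concern.** A change score without a baseline term fixes the slope on baseline at 1. When the baseline-to-post correlation is below 1, the best slope is lower, and the fixed slope leaves avoidable noise in the estimate. The covariate that would remove this noise has already been measured for every outcome. For weight status the plan takes it out by an explicit rule, which is not silence that an unseen analysis plan might fill. What is at stake is precision: a wider interval than necessary for the arm contrast in a trial with twelve sites.

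**Working it through.** **Inputs**

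- From the power paragraph: SD 1.03 ("between-subject variation is normally distributed with a standard deviation of 1.03"), target difference 0.5, one-sided alpha 0.05, 20 recruited per site with 20% attrition, and "between-site variation (nested within treatment group) is negligible".
- From Research design: 12 sites in three groups. Equal allocation is assumed here, giving 4 sites, 80 recruited and 64 analysed children per arm (16 per site).
- Assumed because not given: rho, and any between-site variance in change.

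**The plan's own figure.** Power = Φ(0.5 / (SD × √(2/n)) − 1.645). With SD 1.03 and n = 64, this is Φ(2.746 − 1.645) = 86.5%, not the stated 70% or so. With n = 80 and SD 1.03 × √2 (that is, 1.03 as the SD at each visit and rho = 0) it is 70.1%. The figure can thus be reached only with assumptions that the article does not state. That is a separate matter. It bears on this point only because the article does not say whether 1.03 is the SD of the level or of the change.

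**Residual variance.** Let s be the SD at each visit, equal at both.

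- Change score: 2s²(1 − rho)
- Baseline-adjusted: s²(1 − rho²)
- Ratio: (1 + rho)/2

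**Dilution by site variance.** Suppose 5% of the variance in change lies between sites (an assumption) and adjustment does not touch it. With 16 children per site, the variance of an arm mean is proportional to 0.05 + 0.95/16 = 0.1094. The within-site share is 0.0594/0.1094 = 0.543, so each gain in the arm contrast is multiplied by 0.543.

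| rho (assumed) | Within-site variance reduction | Reduction in arm contrast, 5% between sites | Power after adjustment, if 1.03 is the SD of change, n = 64, no site variance (86.5% before) |
|---|---|---|---|
| 0.3 | 35% | 19.0% | 96.1% |
| 0.5 | 25% | 13.6% | 93.6% |
| 0.7 | 15% | 8.1% | 90.9% |
| 0.9 | 5% | 2.7% | 88.0% |
| 0.95 | 2.5% | 1.4% | 87.2% |

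**What 1.03 would imply for rho.** If 1.03 is the SD of change and the level SD is 1.0 to 1.2 (assumed), then rho = 1 − 1.0609/(2s²) = 0.47 to 0.63, and the zBMI gain is about 27% to 18%. If 1.03 is the SD of the level, the article says nothing about rho. At 0.9 or above the zBMI gain is 5% or less.

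**The same loss, given an imbalance.** Relative to the adjusted estimate, the change-score estimate moves by −(1 − rho) times the baseline difference between arms. With level SD 1.03, 64 per arm and no clustering, the SD of that chance difference is 1.03 × √(2/64) = 0.182. A difference of that size shifts the zBMI contrast by 0.091 at rho 0.5, 0.055 at 0.7, 0.018 at 0.9 and 0.009 at 0.95, against the target of 0.5.

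This is not an additional harm: 2(1 − rho) − (1 − rho²) = (1 − rho)². The excess variance of the change score is exactly the squared multiplier on the baseline difference.

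**The case against.** The best defence is that the planned analysis is legitimate. Several stronger readings are tempting, and the document does not support them.

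- **That the estimate is biased or confounded with regression to the mean.** Sites are randomised. Over repeated randomisations the change-score contrast is unbiased, and the larger standard error already contains the effect of chance imbalance. The shift exists only conditional on a realised difference. At rho 0.5, a 0.2 SD imbalance shifts the result by 0.10 SD, which is 0.57 of the change score's standard error of 0.177 SD (64 per arm, no clustering). This part of the defence stands.
- **That adjustment is worth a third more children.** The factor 1/0.75 = 1.33 requires rho = 0.5 and no between-site variance in change. The plan does assume negligible site variance, but with few sites even a modest amount cuts the gain, as the table shows.
- **That the gain is large for the outcome used for power.** The article gives no rho. If zBMI is highly stable over 8 weeks, the gain is trivial. Moderate correlations are more plausible for diet recall, affect and self-efficacy, but that too is an assumption.
- **That the non-weight outcomes will certainly go unadjusted.** The covariate list is not stated to be exhaustive, and an unseen analysis plan may add the own baseline. Only the weight-status exclusion is fixed in writing.
- **That the zBMI covariate does not exist for caregivers.** Enrolment is by child-caregiver dyad, so the child's value is a natural reading. The wording needs clarifying, no more.

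The explicit exclusion still stands. For any rho below 1, with equal variances at the two visits, leaving out the own baseline costs within-site precision and gains nothing.

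**Conclusion.** The point holds as one of efficiency. The plan analyses change, removes baseline zBMI from the weight-status models by rule, and names no own-baseline term elsewhere. The loss is a factor of (1+rho)/2 in within-site residual variance, assuming equal variances at both visits. Its size cannot be settled from the article: it ranges from a few per cent at rho of 0.9 or more to a quarter at 0.5, and less in the arm contrast if sites differ in change. Confidence is highest for the weight-status models, where the text is explicit, although the numerical gain may be smallest there. It is lower for the other outcomes, where the text is silent. This is a worthwhile improvement to a valid choice, not the correction of a biased analysis.

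**What to change.** In the Data analysis section:

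1. State that each child and caregiver mixed model includes the baseline value of the outcome being analysed.
2. Delete the exclusion for weight-status models, so that baseline zBMI enters the zBMI model. Name baseline waist z-score for the waist model.
3. For caregiver models, use the caregiver's own baseline value of the outcome, and say whether the baseline zBMI covariate means the child's value.

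The response can remain change: with the baseline in the model, the estimated arm effect is the same as when the post-intervention value is modelled, so the hypotheses need no rewording. The cost is one parameter per model and a few words of text, with no new data. Settling this before outcomes are compared by arm also prevents a later choice between adjusted and unadjusted results.
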